#### Secondary analyses

For secondary outcomes of incidence, the same approach as described above will be used to generate CIRs or adjusted CIRs (aCIRs). For the outcome of clinical malaria, Kaplan–Meier survival curves will be produced. If survival is proportional between study arms, a time to event analysis using Cox proportional regression analysis will be conducted to estimate hazards ratios (HR). For outcomes with continuous variables, a linear regression will be conducted. For prevalence outcomes, log-binomial models will be fit to estimate prevalence ratios (PR). A modified Poisson regression with robust standard errors may be used if log-binomial models do not converge. For longitudinally measured outcomes (e.g., parasite prevalence, serology measures, refusal rates), generalized mixed-effect models will be constructed where participant/cluster random effects are included to account for correlation among observations from the same subjects and to account for the clustered study design. Intra-cluster correlation coefficients will be reported from these models. Time-intervention interaction will be evaluated to assess difference in trend between arms. Key subgroup analyses such as age, sex, baseline transmission intensity, distance to Iquitos, distance to a health post, and population size will be performed. All estimators that result from these models will be reported with corresponding 95% confidence intervals and p-values.

Per-protocol analyses will be restricted to clusters in which at least 80% of interventions were delivered according to the study protocol. Analyses will use g-methods, which are generalized methods that separately adjust for baseline and post-treatment covariates associated with participants not adhering to treatment [74].

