### Procedures

#### Enrollment and a baseline assessment

Individual written informed consent will be sought during the baseline survey or during subsequent surveys for new participants. Verbal consent will be requested separately for each subsequent study procedure, including completion of questionnaires, blood testing, and drug administration. Consent for minors less than 18 years of age will be sought from a parent or guardian, and minor assent will also be sought from participants 8–17 years old. Informed consent will be sought in Spanish.

Enrollment and a baseline assessment in consenting individuals will be sought prior to any intervention implementation activities. At the baseline assessment, demographic, epidemiological, and clinical data will be collected. A finger prick will be conducted for rapid G6PD testing using the STANDARD G6PD test (SD Biosensor, Inc., Suwon, South Korea) per manufacturer’s instructions. G6PD status will be categorized as deficient ($$\le$$ 4.0 IU/g Hb), intermediate (4.1–6.0 IU/g Hb), or normal (≥ 6.1 IU/g Hb), which reflect ranges of enzymatic activity below or near normal activity of 9.0 IU/g Hb [31], respectively. As the STANDARD G6PD test includes a hemoglobin (Hb) measurement, this result will also be recorded. Blood from the same finger prick will also be used to generate a dried blood spot (DBS) for malaria molecular testing and G6PD sequencing to identify variants among G6PD deficient and intermediate individuals and 5% of the G6PD normal individuals. For individuals with fever in the past 48 h, microscopy will be performed by health promoters at health establishments, and treatment will be provided per national policy. Current first-line treatment is artesunate-mefloquine for *P. falciparum* and chloroquine (CQ, 10 mg/kg on days 1 and 2, and 5 mg/kg on day 3) plus PQ (0.5 mg/kg/day × 7 days) for *P. vivax* [32].

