## Outcomes and measures

### Sample sizes and power calculations

The study is designed to have 80% power to detect at least 68% relative reduction in cumulative *P. vivax* incidence for fMDA versus control over 3 years, with 15 clusters per study arm (mean population per cluster = 251), based on anticipated baseline *P. vivax* API of 65 cases/1000 population for the control arm, a coefficient of variation (*k*) of 0.87 based on past data, and a 0.05 significance level using a two-sided test [69]. As Peru is aiming for malaria elimination, this anticipated effect size is considered necessary and consistent with available evidence [18–20, 70, 71].

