## Discussion

### Potential challenges

A key challenge that may be encountered is ensuring high coverage of the intervention. Community members may be gone for days at a time working in the field, sleep in multiple homes, or live most of the time in the city of Iquitos. To maximize coverage of fMDA, medications will be delivered door-to-door by DOT at times convenient to the participant. Villagers that miss the first round of fMDA in a cycle or become eligible between the first round and second round will be re-considered for fMDA eligibility prior to the subsequent cycle.

Capturing all incident cases of malaria is also challenging. Participants may not seek care when they feel ill or may have an asymptomatic malaria infection. In order to capture as many cases as possible, households will be visited on a monthly basis by the field team to inquire about symptom onset or case diagnosis. Case report forms used to collect these data are include clear, time-anchored prompts that help participants accurately recall events to reduce recall bias. DBS samples will be collected from all study participants at two timepoints (baseline and endline surveys) which may aid in the detection of subclinical infections. Participants will be encouraged to seek care if they feel ill during the study.

The study communities in which we will intervene are dynamic and mobile in nature. The platform QField will be used to update maps of the study communities each visit and participants will be asked during monthly household surveillance if any individuals in their home are new or have left. In this way, population estimates will be maintained as accurately as possible.

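### Neither analysis named for the survey prevalence outcomes is stated to be the endline contrast adjusted for the village's own baseline value: some precision is lost on secondary outcomes, without bias

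*Protocol article*

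**What the plan says.** The Secondary analyses section of the protocol article gives two analyses for the same survey outcomes.

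- Prevalence ratio: "For prevalence outcomes, log-binomial models will be fit to estimate prevalence ratios (PR", with modified Poisson regression and robust standard errors as the fallback. No covariate is named and none is excluded.
- Longitudinal model: parasite prevalence and serology are listed as repeatedly measured outcomes for generalized mixed-effect models with participant/cluster random effects, and "Time-intervention interaction will be evaluated to assess difference in trend between arms".

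The section does not say which of the two supplies the endline effect. Incidence is treated differently. The Primary analysis section adjusts for baseline incidence and the other restricted-randomization covariates, and Secondary analyses carries that approach over to secondary incidence outcomes only.

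Pre-intervention infection status is measured. Under Enrollment and a baseline assessment: "Blood from the same finger prick will also be used to generate a dried blood spot (DBS) for malaria molecular testing". Under Potential challenges: "DBS samples will be collected from all study participants at two timepoints (baseline and endline surveys".

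Baseline serology is less clear. The enrolment section lists molecular testing and G6PD sequencing as uses of the baseline spot. Serological methods refers to survey samples without naming the baseline survey, though it plans a longitudinal analysis within individuals.

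**The concern.** Infection prevalence and seroprevalence are the outcomes that would show whether the subclinical reservoir shrank. With 15 villages per arm, differences between villages contribute much of the standard error. Where a village's level before treatment predicts its level afterwards, that part can be removed with data already in hand.

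Neither named analysis is stated to do this. The prevalence ratio carries no baseline term. The interaction does use earlier values if baseline is one of the time points, but as a difference in change, which is less efficient than adjusting for baseline. Prior-year reported incidence, even if added, is only a proxy for a largely subclinical prevalence and for antibodies that partly reflect older exposure.

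**Working it through.** **1. The plan's own figure.** The only precision statement concerns incidence: "The study is designed to have 80% power to detect at least 68% relative reduction in cumulative" incidence, "with 15 clusters per study arm (mean population per cluster = 251", "API of 65 cases/1000 population for the control arm", and k "of 0.87 based on past data, and a 0.05 significance level using a two-sided test". The standard unmatched cluster formula for rates, with λ0 = 0.065, λ1 = 0.32 × 0.065 = 0.0208 and y = 251 × 3 = 753 person-years, gives

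c = (1.96 + 0.84)² × [(λ0 + λ1)/y + k²(λ0² + λ1²)] / (λ0 − λ1)² = 14.62, so 15 per arm.

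With the customary extra cluster it is 15.62, and power at 15 per arm is 78.3%. The figure reproduces, but it does not bear on the survey outcomes, for which no power is stated.

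**2. Three ways to use the baseline.** Take village-level values with equal variance at both surveys and correlation ρ. Relative to the endline-only contrast (variance 1), the difference in change has variance 2(1 − ρ) and the baseline-adjusted contrast 1 − ρ². The ratio of these two is 2(1 − ρ)/(1 − ρ²) = 2/(1 + ρ).

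| ρ | variance, change ÷ adjusted | SE saved by adjusting, 1 − √((1 + ρ)/2) |
|---|---|---|
| 0.5 | 1.33 | 13% |
| 0.7 | 1.18 | 8% |
| 0.9 | 1.05 | 2.5% |

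A simulation with 15 villages per arm and 4,000 runs per setting gives the SE relative to endline-only:

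| ρ | change | baseline-adjusted |
|---|---|---|
| 0 | 1.40 | 1.01 |
| 0.3 | 1.21 | 0.98 |
| 0.5 | 1.01 | 0.89 |
| 0.7 | 0.78 | 0.73 |
| 0.8 | 0.62 | 0.60 |

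The change contrast beats endline-only only above ρ of about 0.5. Baseline adjustment costs about 1% when the baseline carries no information.

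**3. Gain beyond prior-year incidence.** Assumptions, none from the article: 150 people sampled per village; correlation 0.6 between baseline log prevalence and prior-year incidence; PCR prevalence 10% with CV 0.87 and a true 50% reduction; seroprevalence 40% with CV 0.5 and a true 30% reduction. Both models adjust for prior-year incidence, and the second adds the baseline survey value. There were 2,000 simulated trials per setting, analysed by village-level regression of log prevalence with t inference.

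| Outcome | ρ | SD of log ratio | SE cut | Power |
|---|---|---|---|---|
| PCR | 0.5 | 0.308 → 0.302 | 2% | 59 → 62% |
| PCR | 0.7 | 0.295 → 0.269 | 9% | 63 → 71% |
| PCR | 0.9 | 0.277 → 0.221 | 20% | 67 → 86% |
| Serology | 0.5 | 0.177 → 0.166 | 6% | 49 → 54% |
| Serology | 0.7 | 0.165 → 0.142 | 14% | 53 → 68% |
| Serology | 0.9 | 0.156 → 0.102 | 35% | 60 → 93% |

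A repeat run agreed within a few points of power. In that run, at ρ = 0.5, the change contrast had less power than leaving the survey baseline out (serology 49% against 52%, PCR 51% against 59%).

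**4. Villages with no positives.** A plain logit of village prevalence is undefined at zero. If prevalence is gamma-distributed with mean 0.10 and CV 0.87, the shape is 1/0.87² = 1.32, and P(zero of 150) = (1 + 150 × 0.10 × 0.87²)^(−1.32) ≈ 0.036. Over 30 villages that is about one, so the covariate needs a zero-safe form.

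**The case against.** The strongest reply is that silence is not exclusion. This is a condensed article, the analysis plan is not shown, and covariate lists for secondary models are commonly left to it. A reader might infer from the bare prevalence-ratio sentence that the trial ignores its baseline survey and throws the precision away. The documents do not support that. The same section plans longitudinal models for these very outcomes, and baseline is the natural first time point, although the section does not say so. Nor does the text rule out a log link in the mixed model, which would give a ratio, or make the interaction the effect estimate.

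The comparator also matters. The larger gains in step 3 are against a model with no survey baseline. Where the correlation is high, even the change contrast captures most of the gain (0.78 against 0.73 at 0.7, 0.62 against 0.60 at 0.8). Where it is low, adjustment adds little over a prevalence ratio without it. The simulation uses village-level regression rather than the planned log-binomial model. Baseline serology, which supplies the largest figures, is only implied.

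All of this stands and limits the point. What remains is that the article names a prevalence-ratio model and an interaction contrast for the same outcomes, gives incidence its own baseline covariate in words, and states for neither survey analysis that it is the baseline-adjusted endline contrast.

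**Conclusion.** The point holds as an efficiency suggestion for secondary outcomes. A reader might go further and infer that an endline prevalence ratio without baseline adjustment is invalid. It is not: randomization makes it a valid comparison, and no bias or misstatement is shown.

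Against a ratio adjusted only for prior-year incidence, the standard error falls by about 2–6%, 9–14% and 20–35% at correlations of 0.5, 0.7 and 0.9 (PCR prevalence at the lower end, serology at the upper). Against the change contrast it falls by about 13%, 8% and 2.5%. At a correlation of 0.3 the simulated gain over an endline-only contrast is about 2%. The size therefore depends on an undocumented correlation and on assumed prevalence and variation. The serology figures also require that the baseline spots are assayed. Priority: optional, a free improvement.

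**What to change.** State that each interim and endline prevalence ratio is adjusted for the village's baseline survey value of the same outcome, next to the restricted-randomization covariates and with clustering accounted for. Use a form that tolerates zero positives, such as the logit of (positives + 0.5)/(n + 1) or an empirical-Bayes prevalence. A village-level covariate also serves participants who enrol after baseline and have no baseline spot of their own.

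Equivalently, constrain the mixed model to a common baseline mean in both arms and report its endline contrast as the effect. Either way, name the one analysis that gives the endline effect before unblinding. Apply the same rule to seroprevalence and antibody level (mean log level as covariate) where baseline spots are assayed for serology.

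The cost is one sentence and one cluster-level degree of freedom: 30 villages less intercept, arm and four covariates leaves 24, which becomes 23. For infection prevalence no new data are needed. For serology that is true only if baseline assays are already planned.

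### The time-by-intervention test for infection prevalence and serology names participant and cluster random effects but no cluster-by-time term; read as random intercepts, it leaves village-level drift out of its standard error

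*Protocol article*

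**What the plan says.** Secondary analyses in the protocol article covers outcomes measured more than once and gives parasite prevalence, serology measures and refusal rates as examples. For these, "generalized mixed-effect models will be constructed where participant/cluster random effects are included to account for correlation among observations from the same subjects"; the same sentence adds that the effects also account for the clustered design. Intra-cluster correlations are to be reported from these models. The text continues: "Time-intervention interaction will be evaluated to assess difference in trend between arms". All estimates come with 95% confidence intervals and p-values.

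No cluster-by-time random effect, random cluster slope or cluster-level degrees of freedom is named for this test. The text does not say that the effects are intercepts only.

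Blood spots are taken from all participants at baseline and endline (Potential challenges), and the interim survey covers a sample (Interim and endline cross-sectional surveys). The only between-village variation quoted is for the primary incidence outcome: "a coefficient of variation (*k*) of 0.87 based on past data" (Sample sizes and power calculations).

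**The concern.** A village effect that is constant over time cancels out of the change from baseline to endline. With random intercepts only, the standard error of the interaction therefore comes from person-level variation, over several thousand people, although 30 villages were randomised. The null being tested becomes no arm difference in trend and, in addition, a common time course for every village in an arm.

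The second condition is unlikely here. Outbreak response follows a sustained rise in cases (Fig. 1 caption). Spraying is intermittent with incomplete household coverage, and nets arrive about every three years (Standard malaria interventions). Communities are mobile (Potential challenges). Initial enrolment ran from October 2024 to March 2025 (Trial status), so baselines may fall at different points of the year. fMDA itself reaches people near recent index cases, so its intensity should differ between intervention villages.

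Infection prevalence and seroprevalence are named secondary outcomes, and the stated hypothesis is that a smaller hypnozoite reservoir will lower both (Aims and objectives). A falsely significant trend difference would be read as support for that.

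**Working it through.** **The plan's own figure.** The article gives no error rate for the interaction test. Its only related figure is "80% power to detect at least 68% relative reduction in cumulative" incidence, with 15 clusters per arm, mean population 251, and "API of 65 cases/1000 population for the control arm". The Hayes–Bennett formula for an unmatched cluster trial is

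c = a + (z_α/2 + z_β)² [(λ0 + λ1)/y + k²(λ0² + λ1²)] / (λ0 − λ1)²

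with λ0 = 0.065, λ1 = 0.065 × 0.32 = 0.0208, y = 251 × 3 = 753 person-years and k = 0.87.

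- Bracket: 0.0858/753 + 0.7569 × 0.004658 = 0.000114 + 0.003525 = 0.003639.
- Divided by 0.0442² = 0.001954: 1.863. Times 7.85: 14.6.
- With a = 0, c = 14.6 and 15 clusters give 81.0% power. With a = 1, c = 15.6 and power is 78.3%. The stated 80% is reproduced.

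**Variance of the interaction.** Write a village's log odds at each survey as a constant part plus a part specific to that survey. Let σ² be the total village variance and CAC the share that is constant, which is the correlation of a village's level between surveys. With two surveys, m people per village, prevalence p and 15 villages per arm, treating sampling error as independent between surveys:

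- True variance of the arm difference in change: (4/15) × [(1 − CAC)σ² + 1/(m p(1 − p))].
- Variance under village intercepts only: (4/15) × [1/(m p(1 − p))].
- Ratio R = 1 + (1 − CAC)σ² m p(1 − p), and type I error = 2[1 − Φ(1.96/√R)].

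**Inputs.** σ² = ln(1 + 0.87²) = 0.56 is borrowed from the incidence k; applying it to prevalence is an assumption. CAC, p and m are also assumed, apart from the mean village population of 251.

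**Worked case.** p = 10%, m = 200, CAC = 0.9. Drift variance is 0.1 × 0.56 = 0.056. Sampling variance is 1/(200 × 0.1 × 0.9) = 0.056. So R = 2, 1.96/√2 = 1.386, and type I error is about 17%.

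**Simulation.** Null trials with 30 villages and two surveys, likelihood-ratio test of the interaction at 5%; 400 trials per cell for the cluster-intercept model and 300 for the model with participant and cluster intercepts (Monte Carlo standard error at most about 3 points). Rejection rates in percent:

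| Prevalence, people per village | Method | CAC 1 | 0.95 | 0.9 | 0.8 | 0.5 |
|---|---|---|---|---|---|---|
| 5%, 150 | closed form | 5 | 7 | 10 | 14 | 26 |
| | cluster intercept | 4–6 | 7 | 9 | 16 | 27 |
| | participant + cluster | 6 | – | 13 | 21 | 35 |
| 10%, 200 | closed form | 5 | 11 | 17 | 26 | 43 |
| | cluster intercept | 4–6 | 12 | 20 | 30 | 50 |
| | participant + cluster | 4 | – | 18 | 31 | 48 |
| 20%, 251 | closed form | 5 | 18 | 28 | 40 | 58 |
| | cluster intercept | 4–6 | 21 | 33 | 40 | 58 |
| | participant + cluster | 6 | – | 30 | 39 | 58 |

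The entry 4–6 is the range over all no-drift settings. In the participant-plus-cluster rows the stated prevalence is that at zero random effects, so average prevalence is somewhat higher. Prevalence and village sample rise together down the table.

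- A participant random effect does not cure the problem.
- Continuous serology (ICC 0.02–0.10, 75–251 per village, CAC 0.95–0.5): 7–70%.
- Lower end: at 2% prevalence the closed form gives 5.2–21% (75–251 per village, CAC 0.98–0.5).
- A t-test on the village-level changes (28 degrees of freedom) stayed at 3–6% in every simulated setting.

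**The case against.** The strongest reply is that the article does not fix the structure. A random cluster slope or a cluster-by-survey effect is itself a cluster random effect, intra-cluster correlations can be reported from such models, and exact covariance structure is often left to an analysis plan. This stands in part: a reader might infer that the plan commits to intercepts only, and it does not say so. But the article is not silent either. It names the random effects, says they deal with clustering, and names the test that they must support, without the one term that this test needs.

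A reader might also take a single inflation range as a property of the trial. The documents do not support that. They give no survey prevalence, ICC or CAC; the k of 0.87 describes reported incidence; and no passage quantifies village drift. With low prevalence and small drift the excess is modest: 7–9% at 5% prevalence, 150 people per village and CAC 0.95–0.9.

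Nor does the point extend to refusal, although it is listed among the longitudinal outcomes. Acceptability, measured as refusal, is assessed in the intervention arm, so there is no between-arm trend in fMDA refusal to test.

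Finally, the interaction is not the only analysis of prevalence, since prevalence ratios are also planned, and nothing makes it the main evidence on the subclinical reservoir. That limits the consequence but leaves the stated test as it is.

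**Conclusion.** The point holds conditionally, for infection prevalence and serology. If the named effects are random intercepts, the time-by-intervention test is anti-conservative and its interval too narrow whenever villages differ in their time course. Under the assumptions above and CAC from 0.95 to 0.5, type I error with a cluster intercept is about 7–27% at 5% prevalence, 12–50% at 10% and 21–58% at 20%, against 4–6% with no drift. These are assumption-based ranges. The direction and mechanism follow from the model; the size cannot be known before the surveys are analysed.

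A reader might infer that the trial's main result is at risk. It is not: the primary analysis uses one case count per village and is unaffected. The point is worth acting on because the secondary test is stated, reported with p-values, and cheap to correct.

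**What to change.** In Secondary analyses, state that the time-by-intervention models for prevalence and serology include a cluster-by-survey random effect, or a random cluster slope for time, and that the interaction is tested on cluster-level degrees of freedom (30 villages − 2 arms = 28). Alternatively, compare the 30 village-level changes from baseline between arms. Only this second option was simulated, and it held 3–6%; the mixed-model option targets the same variance but was not itself run. If an analysis plan already contains such a term, saying so in the protocol is enough.

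The cost is one sentence, one variance term and wider confidence intervals for the trend comparison. No new data are needed.
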